### Concealment mechanism {16b}

To ensure allocation concealment the permuted block sizes will not be disclosed until all practices have been recruited and randomly allocated to the trial arms and patient data has been extracted from the EHR and linked to the NCSR data. The statistician (PC) randomising the general practices will be blinded to the identity of the participating general practices by using unique codes for each practice and will not be involved in the trial recruitment and data collection. Uninformative codes 1, 2 or 3 will be used for the trial arm allocation. Prior to random allocation, the project officers will randomly assign the uninformative codes to each of the trial arms and keep it securely stored and not disclose the key to the statisticians or the Steering committee group.

### Implementation {16c}

Following general practices' consent, and after patient data extraction from the EHR and linkage with NCSR records, the statistician (PC) will randomly allocate the general practice using the random allocation schedule and inform the project officers of the randomisation status of each general practice using the uninformative codes. Using the key for the uninformative codes, the project officers will inform the practice manager of each general practice their allocated study arm allocation both verbally and in writing. The project officers will keep a record of the practice’s unique identifier code, practice name and allocated trial arm status, which will be securely stored and only accessible by the project officers.

## Assignment of interventions: blinding

### Who will be blinded {17a}

The statisticians and the SMARTERscreen steering group members not involved in the delivery of the intervention will be masked to the general practices allocated trial arm until after the analysis of the primary outcome. General practice staff will not be blinded as to the allocation of the randomisation as this will not be possible.

### Procedure for unblinding if needed {17b}

The SMARTERscreen steering group will be unblinded as to the trial arm status code only after all the primary outcome data have been collected and analysed.

## Data collection and management

### Plans for assessment and collection of outcomes {18a}

We have developed a novel method for collecting the outcome data from the NCSR. Lists of eligible patients will be collected from general practice EHR, the NCSR will then add the dates for when each patient’s SMS will be due according to their records, and then at the end of the intervention period, the NCSR will provide the date that each patient’s kit was returned, if returned. The NCSR will send the dataset back to the general practice and a second dataset with all identifying data removed will be securely provided to the research team for analysis (Fig. 4). Depending on the NCSR capacity, to reduce the workload for the general practice and minimise risk for data errors, the de-identified dataset for analysis may be generated by NCSR and securely provided to the investigators for analysis.

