### Hypotheses

Our primary hypotheses are:A GP practice-endorsed SMS sent from general practice to patients aged between 49 and 60 years old and due for a NBCSP kit will increase the proportion of patients who return the NBCSP kit within 6 months of when their kit is sent compared to usual care;A SMS bundle with a GP endorsement of the NBCSP and additional material (i.e. motivational and instructional videos) from general practice to patients aged between 49 and 60 years old and due for a NBCSP kit will increase the proportion of patients who return the NBCSP kit within 6 months of when their kit is sent compared to usual care;Proportion of general practice patients who return the NBCSP kit within 6 months of when the kit was due will differ between patients aged between 49 and 60 years old and due for a NBCSP kit who receive SMS bundle with a GP endorsement of the NBCSP and additional material (i.e. motivational and instructional videos) compared to those who receive an SMS with only GP endorsement of the NBCSP.

Secondary hypotheses:

Sending a GP practice-endorsed SMS with/without additional motivational material to people before their kit is sent will be cost-effective compared with usual care.

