#### Outcomes {12}

The primary outcome is the difference in all three pair-wise comparisons between the three arms in the proportion of eligible patients who were sent a NBCSP kit and who have a date recorded for when the FIT kit was received by the NBCSP and recorded in the NCSR (indicating they have returned their kit) within 6 months from the date when the kit was due to be sent to each participant. For patients who were sent the NBCSP kit, the outcome variable will be coded as having either a ‘FIT kit returned’ or ‘FIT kit not returned’. ‘FIT kit returned’ will include patients who have a date for the returned NBCSP kit in the NCSR registry within 6 months of when their kit was due. ‘FIT kit not returned’ will include patients who were sent a kit but they either do not have a date recorded, or the date is outside the 6-month range. After randomisation has occurred, patients who were eligible to receive a NBCSP kit at the beginning of the intervention period but were subsequently not sent a FIT kit during the trial intervention period will be coded as ‘FIT kit not sent’. This will include patients who were not sent a kit during the 6-month intervention period for a number of reasons: (a) they opted out of receiving kits from the NBCSP; (b) they put their NBCSP kits on temporary hold; (c) they have a recently recorded bowel cancer diagnosis; (d) they have recently had a colonoscopy (and are not due screening); or (e) they have a record of having had a recent FIT test elsewhere. These people will be considered ineligible.

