The intervention period will be for 6 months (26 weeks). The staff (funded by the research team) in the NCSR will then generate datasets for each week of the intervention period that include all patients who are due a SMS that week based on ‘Date SMS is due’ (Dataset 4). This date will be calculated so that the SMS will be sent on a Sunday for kits due 3 days on either side of that date. Each dataset will only include the Unique Record ID, Patient’s first name, and mobile number. The name of the file will identify the GP practice and the date when the SMS are due to be sent. All 26 NCSR datasets created for each general practice will be saved as separate encrypted.csv files and sent using a secure file transfer portal to the general practice.

The general practices in the intervention arms will be instructed to transfer the NCSR.csv datasets that have been separated into 26 weekly files. These will then be uploaded to the GoShare platform and scheduled for sending the SMS/SMS plus bundle on the Sunday they are due (approximately 2 weeks prior to the kit being sent). The control arm practices will not be provided access to the NCSR datasets until the end of the trial.

##### Step 6

At the end of the intervention period:

Using the Dataset 3 created in Step 5, the NCSR will add an additional variable ‘Date the kit was returned’ for each person. If there is no date for a returned kit, then a reason as to why the person was not sent the kit will be added in a separate field—this will happen if there has been a concurrent event (e.g. patient had a colonoscopy, opted out or deferred their screening, was diagnosed with colorectal cancer, or had a FIT test from elsewhere recorded), or the field will be left blank with the assumption that the person did not return the kit within 6 months of the due date of the NBCSP kit. The NCSR dataset (Dataset 5) with the added kit return dates will be stored on the NCSR secure server as a.csv dataset and downloaded by secure file transfer by the practice when needed.

##### Step 7

Dataset 6 will be created using Dataset 5, where individual identifying information (such as name, address, and mobile number) will be removed, and provided to the research team for analysis. The dataset may be securely transferred to the research team via the GP Practice (once the records have been de-identified) or directly from NCSR.

##### Step 8

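### Return dates are extracted at the end of the 26-week intervention period, before the 6-month outcome window has closed, and blanks are coded as non-return

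*Protocol article*

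**What the plan says.** - **Outcome definition.** Outcomes {12} counts a kit as returned if the register holds a return date "within 6 months from the date when the kit was due to be sent to each participant". A patient who was sent a kit but has no date, or a date outside that range, is coded as not returned.
- **SMS schedule.** Steps 4 and 5 of the method set the SMS date at the kit due date minus 14 days. They fix an intervention period of 26 weeks with one SMS file per week: "All 26 NCSR datasets created for each general practice will be saved as separate encrypted.csv files". There is a small tolerance: "the SMS will be sent on a Sunday for kits due 3 days on either side of that date".
- **Time of extraction.** The section on collection of outcomes {18a} says "at the end of the intervention period, the NCSR will provide the date that each" patient's kit was returned. Step 6 opens with the same timing.
- **Rule for blanks.** Under Step 6, if there is no return date and no recorded reason for not sending a kit, the field is "left blank with the assumption that the person did not return the kit within 6 months of the due date of the NBCSP kit".
- **Start of the window.** Hypotheses 1 and 2 count "within 6 months of when their kit is sent compared to usual care", as does the abstract. Hypothesis 3, the Objectives, Outcomes {12} and Statistical methods {20a} count from the due date. The fields listed in Steps 4 and 6 include a due date and a return date but no date on which the kit was sent.

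**The concern.** A 6-month outcome needs 6 months of observation after the last patient's window opens. Here the windows open one weekly batch at a time over the whole 26 weeks, and the register is read at the end of those same 26 weeks. The rule for blanks then turns incomplete follow-up into a firm negative.

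Three things are at stake:

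- Participation would be understated in every arm, and absolute differences would shrink with it.
- The SMS is a prompt timed just before the kit arrives, so earlier return is a plausible effect in itself. With a truncated window, earlier return is counted as additional return.
- The arm-specific participation rates feed the Policy1-Bowel model, so the error would carry into the cost-effectiveness and budget-impact results.

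**Working it through.** **Inputs from the protocol**
- Intervention period: 26 weeks. Check: 26 × 7 = 182 days, which agrees with the stated 6 months.
- Weekly SMS batches: w = 0, 1, …, 25 (Step 5).
- SMS to kit due date: 14 days = 2 weeks (Step 4).
- Extraction: week 26 ({18a} and Step 6).
- Required window: 6 months, about 26 weeks, from the due date (Outcomes {12}).
- Planned rates: 34% v 44%, and 44% v 51.5%. Alpha 0.017, ICC 0.01, mean cluster size 260, coefficient of variation 0.76 (Sample size {14}).

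**Step 1: follow-up at extraction.** For batch w, follow-up = 26 − (w + 2) weeks.
- First batch (w = 0): 26 − 2 = 24 weeks, or 168 days (171 with the 3-day tolerance).
- Last batch (w = 25): 26 − 27 = −1 week.
- Mean with equal batches: (24 + (−1)) / 2 = 11.5 weeks.
- Batches with 26 weeks: 0 of 26. Batches with zero or negative follow-up: 2. Batches with under 13 weeks: 14.

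**Step 2: the more favourable reading.** Suppose the kit due dates, rather than the SMS dates, span the 26 weeks. Follow-up is then 26 − w: maximum 26, minimum 1, mean 13.5 weeks. Only the first batch reaches 26 weeks.

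**Step 3: share of 6-month returns captured.** The documents give no return-time distribution, so this step rests on an assumption: among those who return within 6 months, return times are exponential (truncated at 26 weeks), with F(t) = 1 − exp(−t·ln 2 / median). Captured share = mean over batches of F(max(follow-up, 0)) / F(26).

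| Median | Captured, SMS dates span period | 34% reads as | 44% reads as | 10 points reads as | Captured, due dates span period |
|---|---|---|---|---|---|
| 3 weeks | 0.778 | 26.4% | 34.2% | 7.8 | 0.85 |
| 4 weeks | 0.731 | 24.9% | 32.2% | 7.3 | 0.81 |
| 6 weeks | 0.661 | 22.5% | 29.1% | 6.6 | 0.74 |
| 8 weeks | 0.616 | 20.9% | 27.1% | 6.2 | 0.69 |

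**Step 4: power.** Design effect = 1 + ((1 + 0.76²) × 260 − 1) × 0.01 = 5.09. With 20 practices per arm (21 less the spare one), the effective size is 20 × 260 / 5.09 ≈ 1,021 per arm. With full follow-up, power is 0.99 for 34% v 44% and 0.84 for 44% v 51.5%, so the stated sample size is adequate. After truncation with SMS dates spanning the period:

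| Median | Power, 34% v 44% | Power, 44% v 51.5% |
|---|---|---|
| 28 days | 0.90 | 0.58 |
| 42 days | 0.85 | 0.51 |
| 90 days | 0.75 | 0.40 |

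**Step 5: an SMS that changes speed only.** Assume 38% return by 6 months in both arms, and that the SMS shortens the median from 6 to 4 weeks. The observed difference is 38 × (0.731 − 0.661) ≈ 2.6 points, although the true 6-month difference is zero.

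**Step 6: earliest complete extraction.** The last SMS goes out at week 25 and its kits are due at week 27 plus up to 3 days. Adding 26 weeks gives week 53 plus 3 days, so about week 54 after the first SMS, before any recording lag.

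**The case against.** The best defence is that this is loose wording and no truncation is planned. The timeline is in Figs 3 and 4, which are not in the text reviewed, and Fig. 4 is captioned as proposed and subject to change. The text under Fig. 4 says the register adds data at the end of the trial, which is not defined and could be later than week 26. The outcome definition allows for dates beyond the 6-month range, and the blank rule presupposes that the window has passed. Both suggest a later extraction was in mind. That may well be the intention, but it does not remove the conflict. Two separate places give the end of the intervention period, Step 6 is the instruction on which register staff would act, and no follow-up period after the intervention is stated.

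Second, the statement that no patient has 6 months depends on SMS dates spanning the period. That is what Step 5 describes. If due dates span it instead, the first batch reaches 26 weeks, no batch has zero follow-up, and capture rises to 0.85–0.69. The conclusion is unchanged.

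Third, truncation applies to all arms alike, and the size depends on assumed return times. Both points are correct. Equal truncation still biases absolute differences towards zero, and it does not protect against an effect on speed. Even so, power for 34% v 44% stays at 0.75 or above over the range examined.

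Finally, the difference between sent and due as the start of the window is a separate and lesser inconsistency.

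**Conclusion.** The concern holds. The stated extraction time and the rule for blanks cannot deliver the stated primary outcome. This part needs only calendar arithmetic: at week 26, none of the 26 batches has a full window (one of 26 on the favourable reading), and mean follow-up is 11.5 weeks (13.5 on the favourable reading).

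If the extraction were carried out as written, observed participation would fall in every arm. By how much is uncertain, because it depends on return times that the documents do not give. With equal weekly batches and exponential medians of 3 to 8 weeks, 78% to 62% of 6-month returns would be captured. The comparison most exposed is SMS only against SMS bundle, where power falls from 0.84 to between 0.58 and 0.40 for medians of 28 to 90 days.

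Because the error sits in the primary outcome of every arm, it must be corrected before data are extracted.

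**What to change.** 1. In {18a} and Step 6, replace the end of the intervention period with an extraction date no earlier than 6 months after the last kit due date of any listed patient, plus the register's recording lag. That is about 54 weeks plus lag after the first SMS.
2. Code a kit as returned only if its return date lies between the patient's due date and 6 months after it. Treat a blank as non-return only once that window has closed.
3. Use the due date as the start of the window in the abstract and in every hypothesis. It is fixed before randomisation and is already in the dataset.
4. Check Figs 3 and 4 against the corrected timing and align them where they differ.

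The cost is a change of wording and a later register extraction. Data arrive about 6 to 7 months after the end of the intervention period, a delay the stated outcome needs in any case. Sample size, randomisation and intervention delivery are unaffected.

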**Fig. 4 Fig4:**
[figure not shown]
Data collection, dataset names, and timepoints (EHR, electronic health record; GP, general practice; NCSR, National Cancer Screening Register; GoShare, the SMS provider) (Proposed timeline, subject to change.)

The data collection at the general practice will be done within the practice by the practice manager under the guidance of the project officer and with clear instructions and technical support where necessary from the NCSR. The trial will fund a staff member at the NCSR to add the required data to the datasets at the beginning and end of the trial.

The data collection method will be tested in one practice prior to implementing the process.

#### The method (Fig. 4)

##### Step 1

The eligible patient list will be collected from each general practice EHR using a bespoke Structured Query Language (SQL) query. The list will be saved as a comma-separated values (.csv) file securely on the practice computer, with a name specific to the study identifier of the practice (practice ID) and the date of extraction (Dataset 1).

##### Step 2

The practice manager will add three columns of data including (1) a column with a Provider number for the principal GP for that practice, (2) a column with a unique trial ID code for each patient (e.g. GP0010001), and (3) a column with a unique practice ID code for each practice (e.g. GP001) (Dataset 2).

##### Step 3

This dataset will be saved as a.csv file and uploaded to the NCSR using a secure file transfer protocol (SFTP).

##### Step 4

Once the NCSR have the.csv file (Dataset 2), they will match the patients in the NCSR by date of birth, Medicare number, and name. The.csv file will be enriched with five additional columns of data for each person: one for the date they returned their last NBCSP kit (or blank if they have not returned one before) [‘Date_kit_returned’], one with the date their next NBCSP kit is due [‘Date_Kit_Due’], one if the NCSR cannot match patients’ identifying data with the register’s records [‘1’ if records match with NCSR database, ‘0’ if data in the.csv file does not match the register], one calculating the date the SMS will be sent [‘Date SMS is due’ which will be calculated as the (‘Date the NBCSP kit is due’ − 14 days)], and one calculating the patient’s age at the time when their kit is due [‘Age in months when kit is due’, which will be calculated as (= ‘Date the NBCSP kit is due’ − ‘Date of Birth’ in years, multiplied by 12)].

The NCSR will then save a.csv file (i.e. NCSR dataset) for every practice (Dataset 3).

##### Step 5

The intervention period will be for 6 months (26 weeks). The staff (funded by the research team) in the NCSR will then generate datasets for each week of the intervention period that include all patients who are due a SMS that week based on ‘Date SMS is due’ (Dataset 4). This date will be calculated so that the SMS will be sent on a Sunday for kits due 3 days on either side of that date. Each dataset will only include the Unique Record ID, Patient’s first name, and mobile number. The name of the file will identify the GP practice and the date when the SMS are due to be sent. All 26 NCSR datasets created for each general practice will be saved as separate encrypted.csv files and sent using a secure file transfer portal to the general practice.

The general practices in the intervention arms will be instructed to transfer the NCSR.csv datasets that have been separated into 26 weekly files. These will then be uploaded to the GoShare platform and scheduled for sending the SMS/SMS plus bundle on the Sunday they are due (approximately 2 weeks prior to the kit being sent). The control arm practices will not be provided access to the NCSR datasets until the end of the trial.

##### Step 6

At the end of the intervention period:

Using the Dataset 3 created in Step 5, the NCSR will add an additional variable ‘Date the kit was returned’ for each person. If there is no date for a returned kit, then a reason as to why the person was not sent the kit will be added in a separate field—this will happen if there has been a concurrent event (e.g. patient had a colonoscopy, opted out or deferred their screening, was diagnosed with colorectal cancer, or had a FIT test from elsewhere recorded), or the field will be left blank with the assumption that the person did not return the kit within 6 months of the due date of the NBCSP kit. The NCSR dataset (Dataset 5) with the added kit return dates will be stored on the NCSR secure server as a.csv dataset and downloaded by secure file transfer by the practice when needed.

##### Step 7

Dataset 6 will be created using Dataset 5, where individual identifying information (such as name, address, and mobile number) will be removed, and provided to the research team for analysis. The dataset may be securely transferred to the research team via the GP Practice (once the records have been de-identified) or directly from NCSR.

##### Step 8

Data for the measures for adherence to Interventions 1 and 2 (such as the participants who received the SMS opened and/or watched the web-based content) will be downloaded from GoShare platform and merged with Dataset 6 using the unique record ID code created in Step 2. This will be done by the project officers and Healthily.

### Plans to promote participant retention and complete follow-up {18b}

Training, including a comprehensive training manual, and ongoing support will be provided by the project officers for practice staff involved, including informing any new clinical or administrative staff who join the practice during the trial period, about the trial. The practice champion will have contact details for the project officer for their state, and contact details for the ethics committee and senior researchers. If there are any deviations from the trial or problems encountered during the study, the project officers will record them and inform the SMARTERscreen steering group.

### Data management {19}

Data management will be overseen by the project officers and under the supervision of the SMARTERscreen steering group, and statistician in accordance with the statistical analysis plan (SAP). The project officers will be responsible for training and supervising the general practice staff to extract the eligible patient list from the EHR, save it securely, name it according to the naming protocol, upload it to the NCSR, download the revised list from the NCSR, and then upload the de-identified lists with the results to the research staff (Fig. 4). The NCSR staff member will be supervised and overseen by the SMARTERscreen steering group to manage the data at the NCSR including the secure transfer to and from the general practices.

### Confidentiality {27}

All patient data will remain confidential and no identifiable patient information will be included in the final data set that is used for the trial analysis. The only people who will have access to identifiable data will be the general practice staff who already have permission to access these data, and the NCSR who also have permission to access these data. Project officers responsible for assisting and training general practice staff to collect and upload/download patient lists to the NCSR will sign confidentiality agreements between each practice and themselves and be bound by the University of Melbourne Human Research Ethics Committee requirements. Only de-identified data will be provided to the research team at the end of the data collection period with unique identifiers provided for trial participants (Fig. 4).

All general practice consent forms will be scanned and stored in a secure password-protected folder on a secure server at the University of Melbourne and only accessible to the project officer and senior researchers working on the trial. These servers are protected by a VPN and Okta verification. Any paper information will remain strictly confidential and stored in secured locked cabinets in a secure office within the Primary Care Cancer Research Group, Department of General Practice and Primary Care at the University of Melbourne and only accessible to selected researchers working on the trial (TJ, AW, SF, LB, JM). All data will be destroyed 15 years after publication according to the University of Melbourne Office of Research Ethics and Integrity Ethics Committee (OREI).

